### Procedures, recruitment, and randomization

When adenomyosis is suspected on TVUS (see criteria in Table 1) and MRI is performed to confirm adenomyosis (see criteria in Table 2), eligible patients will be informed about the study by the gynecologist, resident, research nurse or study coordinator and will be informed about the website for additional information and an introduction video (Multimedia Appendix 1). If the patient declines randomization, she will be asked to participate in the cohort group. The patients in the cohort study group will be offered standard care (ie, hysterectomy, since embolization is not available outside the trial). Afterwards, participants with written informed consent are randomly allocated (2:1) to the experimental intervention (UAE) or the standard care control group (hysterectomy). Randomization is computer-based and stratified for the participating hospitals. The study is not blinded since uterine artery embolization is performed either under conscious sedation or epidural anesthesia in contrast to a hysterectomy which is performed in the operating room under full narcosis. Therefore, it is not possible to blind the patients or the physicians.

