### Baseline

At time of inclusion and randomization, baseline medical history, obstetric history, and laboratory work up (hemoglobin, renal function (eGFR), CA-125, Anti-Mullerian hormone (AMH) in a subset of centers) are reported in the eCRF. The imaging characteristic displayed in Table 1 will all be registered.

Patients will fill out validated Health-Related Quality of Life (HRQOL) and symptom questionnaires (see "outcome measures")

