### Sample size

This study has a noninferiority design, where UAE is considered noninferior to hysterectomy when HRQOL at 6 months does not differ (delta) more than 5 points (scale 0-100). When the following assumptions are used: SD of 9 points (scale 0-100), alpha 0.10, power 0.80, using a one-sided two-sample equal-variance *t* test, a sample size of 1 x 52 patients (embolization) and 1 x 34 patients (hysterectomy) is needed. Excluding 10% dropout, in total 96 patients are needed for the primary outcome. Assumptions are based on the Embolization versus Hysterectomy (EMMY) trial outcomes [13].

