### Statistical analysis

Analysis of the study will be based on the intention-to-treat and per protocol analysis. With regard to the primary outcome variable (WHOQOL-Bref, SF-12), non-inferiority is established between UAE and hysterectomy when the mean difference does not exceed 5 points (with a SD of 9 points).

The primary outcome will be analyzed using linear mixed modeling, applying transformation if necessary, adjusting for, if necessary, clinically relevant baseline imbalances. With regard to the secondary outcomes, we will use the appropriate nonparametric and parametric statistics to evaluate statistically significant differences between the two treatments. A *P* value <.05 will be considered as statistically significant. In all analyses, statistical uncertainties will be expressed in 90%CI.

The database will be locked 6 months after the last surgical procedure in order to obtain the short-term outcomes. These data will be analyzed and published in a “short term results” manuscript. The long-term results (HRQOL and costs) will be analyzed 12 months after the last procedure, when the last patient returned her last questionnaire.

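### The primary model adjusts by observed, undefined baseline imbalance and may be transformed, with no commitment to baseline HRQOL or hospital and no link from a transformed result to the 5-point margin

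*Protocol article*

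**What the plan says.** All places are in the protocol article.

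- **Statistical analysis**, model: "The primary outcome will be analyzed using linear mixed modeling", then "applying transformation if necessary, adjusting for, if necessary, clinically relevant baseline imbalances". The section does not define necessity or clinical relevance, and it lists no fixed or random terms.
- **Statistical analysis**, criterion: "non-inferiority is established between UAE and hysterectomy when the mean difference does not exceed 5 points (with a SD of 9 points". The Sample size section puts the margin on its scale and at its time point: "HRQOL at 6 months does not differ (delta) more than 5 points (scale 0-100".
- **Baseline**: "Patients will fill out validated Health-Related Quality of Life (HRQOL) and symptom questionnaires". The Follow-up section lists the same questionnaires at baseline and at five later times.
- **Procedures, recruitment, and randomization**: "Randomization is computer-based and stratified for the participating hospitals". The same section explains that neither patients nor physicians can be blinded.
- **Strengths and Limitations** (Discussion): all hysterectomy techniques are allowed, and the technique is to be recorded and allowed for in the analysis.

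**The concern.** The article does not simply leave the covariates to a later document. It states a rule, and the rule has three weaknesses.

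1. **Adjustment is driven by imbalance.** Under randomization a baseline imbalance is a chance event. A covariate is worth including because it predicts the outcome, not because it happens to differ between arms. The baseline value of the outcome and the stratification factor are the two obvious candidates, and the text commits to neither.
2. **The trigger is undefined.** The trial is unblinded and plans 86 evaluable patients. Which model is primary can then be settled after the data are seen.
3. **Transformation is open while the margin is in raw points.** After a non-linear transformation the model estimates a different quantity. The text gives neither a converted margin nor a back-transformation.

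At stake are precision, the calibration of the non-inferiority test, and whether the declared margin is the one actually tested.

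**Working it through.** **Inputs.** From the Sample size section: margin 5, SD 9, 52 and 34 patients, power 80%. From the Statistical analysis section: 90% confidence intervals, which correspond to a one-sided 0.05 test. The correlation ρ between baseline and 6-month HRQOL is not in the document. I assume 0.3, 0.5 and 0.7.

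**Reproducing the plan's figure.** The standard error is 9 × √(1/52 + 1/34) = 9 × 0.2206 = 1.985. The noncentrality is 5/1.985 = 2.52 on 84 degrees of freedom. Noncentral-t power at one-sided 0.05 is 80.3%, and 86/0.9 = 95.6 gives the stated 96. So 52/34 comes from the unadjusted SD. The document words the test as one-sided with alpha 0.10. Read literally, 52/34 would have 89.0% power. That is a separate matter, and one-sided 0.05 is used below because it reproduces the plan.

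**Baseline score always in the model.** Residual SD = 9 × √(1 − ρ²). The 90% half-width is 1.663 × residual SD × 0.2206.

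| ρ (assumed) | Residual SD | Power | 90% CI half-width |
|---|---|---|---|
| 0 (unadjusted) | 9.00 | 80.3% | 3.30 |
| 0.3 | 8.59 | 83.5% | 3.15 |
| 0.5 | 7.79 | 89.3% | 2.86 |
| 0.7 | 6.43 | 96.8% | 2.36 |

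**Adjusting only when imbalanced.** The document gives no trigger, so I assume a difference in baseline means above 0.25 SD. Simulation at 52/34, one-sided 0.05, 20,000 runs per setting. Power is at a true difference of 0, type I error at a true deficit of 5 points. Values are for ρ = 0.3 / 0.5 / 0.7.

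| Rule | Power (%) | Type I error (%) |
|---|---|---|
| Never adjust | 80.5 / 80.6 / 80.5 | 4.9 / 5.0 / 4.8 |
| Adjust if imbalanced | 81.2 / 84.2 / 87.7 | 4.5 / 3.9 / 3.0 |
| Always adjust | 83.2 / 89.2 / 96.8 | 4.9 / 4.8 / 5.1 |
| More favourable of the two models | 85.4 / 90.7 / 97.3 | 6.1 / 7.0 / 7.9 |

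Repeat runs move these by a few tenths of a point. The imbalance-triggered rule is conservative because the unadjusted standard error is kept exactly when the arms are balanced, where it is too large.

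**Transformation.** The document names none. Taking a log for illustration, a 5-point deficit at control mean M is ln((M − 5)/M): ln(45/50) = −0.105 at 50, ln(65/70) = −0.074 at 70, ln(85/90) = −0.057 at 90. Fix the log margin at M = 70 (ratio 65/70) and it means 50 × 5/70 = 3.6 points at a mean of 50 and 90 × 5/70 = 6.4 at 90. For a reflected log of 100 − score, fixed the same way (ratio 35/30), it means 50 × 5/30 = 8.3 points at 50 and 10 × 5/30 = 1.7 at 90. The 5-point margin has no single value on such scales.

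**The case against.** The strongest case is that a condensed article need not list model terms, and that several stronger readings do not hold.

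- **A reader might infer that the plan discards baseline HRQOL and hospital.** It does not say so. A linear mixed model can carry baseline as a covariate or repeated response and hospital as a random intercept. Neither is named and neither is excluded. What stands is that the one adjustment rule the section does state is conditional on imbalance, so a full plan that always adjusts would have to depart from it.
- **A reader might infer that imbalance is the only basis for adjustment.** The Discussion also promises allowance for hysterectomy technique. That does not help: technique is determined after randomization and exists in one arm only.
- **A reader might infer that the rule favours UAE.** As written it looks at baseline data, and under the assumed trigger it is conservative. The inflation to 6.1-7.9% needs a free choice of the better result, which the text does not describe but, lacking a trigger, does not rule out. Omitting a prognostic stratification factor would likewise usually make the standard error too large.
- **A reader might infer that the margin becomes untestable.** A transformed model can be back-transformed to a difference in points, or the margin converted at a stated control mean. What stands is that the article provides for neither.
- **A reader might infer that the trial is underpowered without adjustment.** At 52/34 it reaches 80.3% unadjusted.

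**Conclusion.** The point holds as a weakness in a stated rule; it is not an error in the sample size. Adjustment turns on an undefined imbalance, there is no commitment to the baseline score or the stratification factor, and transformation is permitted without a link to the raw 5-point criterion.

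Relative to the imbalance-triggered rule, always including the baseline score gains about 2, 5 and 9 percentage points of power in the simulation (83.2 − 81.2, 89.2 − 84.2, 96.8 − 87.7) at correlations of 0.3, 0.5 and 0.7, and restores type I error to about 5%. These figures rest on the assumed correlations, the assumed 0.25 SD trigger, normal data, SD 9, the 52/34 split and one-sided 0.05. The gain from including hospital is not quantified, because the document gives no between-hospital variation. The transformation examples rest on assumed control means and an assumed log. The change should be made, but the stated 80% power does not hang on it.

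**What to change.** Replace the sentence on adjustment and transformation with wording to this effect:

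> The primary linear mixed model always includes the baseline value of each HRQOL score analysed as primary (WHOQOL-Bref, SF-12) and hospital (random intercept, or small hospitals pooled), whatever the observed imbalance. Further adjustment for imbalances is a sensitivity analysis only. The non-inferiority test is made on the untransformed 0-100 scale, with robust or bootstrap 90% limits if residuals are skewed. Transformed models are sensitivity analyses.

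The wording refers to each score because the article names two instruments in combination, so there is no single baseline score. Reconcile the Discussion's remark on hysterectomy technique with this by keeping technique out of the primary model.

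The cost is wording in the protocol and analysis plan, plus a few degrees of freedom. No new data are needed, since the baseline questionnaires and hospital are already recorded. The article reports that analysis had not begun at submission. The change should be dated before any outcome data are examined by arm.

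### Secondary differences are judged at P<.05 but shown with 90% CIs, so a result with .05≤P<.10 is non-significant while its interval excludes zero (minor)

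*Protocol article*

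**What the plan says.** All three statements that matter stand in the Statistical analysis section of the protocol article.

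- Secondary outcomes: "we will use the appropriate nonparametric and parametric statistics to evaluate statistically significant differences between the two treatments".
- Threshold: a *P* "value <.05 will be considered as statistically significant". Neither here nor elsewhere does the article say whether this P value is one-sided or two-sided.
- Interval level: "In all analyses, statistical uncertainties will be expressed in 90%CI". Secondary outcomes are not exempted.

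The Sample size section gives the background for the primary outcome: "This study has a noninferiority design", with a margin of 5 points on a 0-100 scale. The planning inputs are "SD of 9 points (scale 0-100), alpha 0.10, power 0.80", "using a one-sided two-sample equal-variance" *t* test. The result is 52 patients for embolization and 34 for hysterectomy, or 96 in total after allowing for 10% dropout.

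**The concern.** A confidence interval and a significance test agree only when their levels are complementary. A 90% interval is a natural companion to a one-sided 5% noninferiority test. A two-sided test of difference at .05 needs a 95% interval. The plan carries the 90% level over to every analysis, including secondary comparisons that have nothing to do with noninferiority.

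At stake is how secondary results will be read. Complications, reinterventions, pain, bleeding and recovery are among the outcomes listed, several at up to five time points. A reader who judges each one by whether its interval crosses zero would be applying a two-sided 10% standard that the plan does not declare. With two standards in the text, emphasis could also drift to whichever of the P value or the interval looks more favourable.

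**Working it through.** **Inputs.** From the Sample size section: SD 9, margin 5, power 0.80, 52 and 34 evaluable patients, 10% dropout. From the Statistical analysis section: P<.05 and 90% CI. Assumed: the secondary tests are two-sided, and SD 9 (the planning value for HRQOL) serves as an illustration for other continuous outcomes.

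**Step 1. Reproduce the plan's own figure.** The size of the smaller group is n = (z_alpha + z_power)² × SD² × (1 + 1/r) / margin², where r is the ratio of embolization to hysterectomy patients, 52/34 = 1.529.

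- One-sided alpha 0.05: (1.645 + 0.842)² × 81 × 1.654 / 25 = 33.1, so 34 hysterectomy and 52 embolization patients, 86 in all. The exact *t* power is 0.803. With dropout, 86/0.90 = 95.6, so 96. This matches the article.
- One-sided alpha 0.10, as printed: (1.282 + 0.842)² × 81 × 1.654 / 25 = 24.2, so 25 + 39 = 64. At 2:1 allocation it is 22 + 44 = 66. Neither matches.

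The stated numbers therefore correspond to one-sided 0.05, which pairs with a 90% CI. One-sided 0.10 would pair with an 80% CI.

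**Step 2. Interval against test.** A two-sided 90% CI excludes zero when |estimate|/SE > 1.645, that is, when two-sided P<.10. Two-sided P<.05 requires |estimate|/SE > 1.960. Results between these two values, .05≤P<.10, are discordant. The width ratio is 1.645/1.960 = 0.839, so 90% intervals are 16% narrower. In reverse, 1.960/1.645 = 1.19.

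**Step 3. Size on the HRQOL scale.** SE = 9 × √(1/52 + 1/34) = 1.985. With 84 degrees of freedom the critical values are 1.663 and 1.989, so the half-widths are:

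- 90% CI: 1.663 × 1.985 = 3.30 points
- 95% CI: 1.989 × 1.985 = 3.95 points

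An observed difference between 3.30 and 3.95 points is non-significant by the rule but has a 90% interval that excludes zero.

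**Step 4. How often.** From the noncentral *t* distribution with 84 degrees of freedom:

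| True difference (points) | P(discordant) | P(90% CI excludes 0) | Discordant share of exclusions |
|---|---|---|---|
| 0 | 5.0% | 10.0% | 50% |
| 2 | 9.4% | 26.3% | 36% |
| 3 | 12.2% | 44.3% | 28% |
| 4 | 12.6% | 63.9% | 20% |
| 5 | 10.1% | 80.3% | 13% |

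The probability of discordance peaks at about 13%, between 3 and 4 points.

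**The case against.** The strongest counter-argument is that sidedness is never stated for P<.05, and the only sidedness in the article is one-sided. A one-sided .05 test would agree with a 90% CI. This stands to the extent that the two-sided reading is an assumption. It remains the natural one, because the secondary tests are meant "to evaluate statistically significant differences between the two treatments" and no direction is given.

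A second argument is that little depends on the mismatch. Significance is set by the P value, and no secondary decision rule uses the interval. That is correct, and it is why the point is minor.

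Three stronger readings are tempting, and the document does not support them:

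- A reader might infer that secondary results in general will contradict their own P values. They do so only when .05≤P<.10. Half of the intervals that exclude zero are discordant when there is no true effect, but the share falls as the effect grows (Step 4). Single-arm outcomes (pathology after hysterectomy, imaging after UAE) fall outside the conflict. The cost-utility analysis may do so too, since no test is named for it.
- A reader might infer that 90% intervals overstate precision. An interval labelled 90% has the coverage it claims. The fault is the mismatch with the declared rule.
- A reader might infer that the 90% CI is also wrong for the primary outcome. The stated sample size reproduces at one-sided 0.05, the level that a 90% CI serves. What is inconsistent there is the printed alpha of 0.10, which is a separate matter to reconcile.

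**Conclusion.** The point holds as a minor inconsistency. On a two-sided reading of P<.05, the plan fixes two levels for secondary between-group comparisons that disagree for every result with .05≤P<.10. The expected frequency is 5% per comparison with no true effect, and up to about 13% in the illustration with 52 versus 34 patients and SD 9. Those percentages above 5% depend on the assumed SD and group sizes; the 5% under no effect does not.

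The secondary significance calls, the primary noninferiority conclusion and the sample size are the same whether or not the interval level is changed. The effect is confined to how secondary estimates are displayed and read.

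**What to change.** In the Statistical analysis section, replace the blanket statement on intervals with two rules: the primary noninferiority comparison is reported with a two-sided 90% CI; secondary between-group comparisons use two-sided P<.05 and are reported with two-sided 95% CIs. If the sponsor does intend one-sided secondary tests, the text should say so and give the direction for each outcome.

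In the same edit, reconcile the primary alpha. The Sample size section prints one-sided 0.10, which pairs with an 80% CI and gives 64 to 66 evaluable patients instead of 86. The stated 52 + 34 and the 90% CI both fit one-sided 0.05. The sponsor should confirm which level was intended, so that the two sections state one alpha. The change to the secondary intervals does not depend on that answer.

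The cost is a short edit in two sections before database lock. Secondary intervals become about 19% wider (for example, half-width 3.95 instead of 3.30 points), and no further patients are needed.

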**Methods:**

This is a multicenter non-blinded randomized controlled trial comparing UAE and hysterectomy. Eligible patients are symptomatic premenopausal women without the desire to conceive and who have symptomatic magnetic resonance imaging (MRI)–confirmed pure adenomyosis or dominant adenomyosis accompanied by fibroids. After obtaining informed consent, patients will be randomly allocated to treatment in a 2:1 UAE versus hysterectomy ratio. The primary objective is HRQOL at 6 months following the assigned intervention. Secondary outcomes are technical results, pain management, clinical outcomes, HRQOL, and cost effectiveness during 2 years of follow-up. In addition, transvaginal ultrasound (TVUS) and MRI will be performed at regular intervals after UAE.

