### Follow-up

The research investigator will send invitations for the digital online secured patient questionnaires by email at baseline, 6 weeks, 3 months, 6 months, 12 months and 24 months of follow-up. All patients will also specifically be asked at baseline to give their consent to be approached for long-term follow up. Validated questionnaires will be filled out to report on HRQOL, symptoms, clinical outcomes, return to normal activities, absence of work, medication use, costs, medical consultation/consumption, and additional received therapy (see “outcome measures”). The patients who underwent UAE will receive a TVUS at 6 weeks and 6 months with an MRI at 6 months to compare the adenomyosis features with baseline results. In the hysterectomy group, pathology outcomes are also registered. All the eCRFs will report complications.

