### Outcomes measures

The primary outcome is quality of life at 6, 12 and 24 months after index procedure as measured by a combination of the World Health Organization Quality of Life Scale (whoqol-Bref) and Short Form-12 (SF-12) Questionnaire.

Secondary outcomes at 6 weeks and 3, 6, 12, 24 months after treatment consists of:

Clinical outcomes: technical failure rate, clinical failure arte as defined by secondary hysterectomy, additional therapy or reinterventions, complications.Recovery related outcomes (6 weeks, 3 and 6 months): hospital stay, return to normal activities (Recovery Index-10).Symptom and quality of life outcomes: menstrual characteristics (pictorial blood assessment chart), validated pain-questionnaire (Numeric Pain Rating Scale 0-100 scale, Facet 1: Pain and discomfort WHOQOL-100), sexual functioning (WHOQOL-100, sexual activity domain), satisfaction (Likert-scale, vignettes preference), quality of life (WHOQOL-Bref, SF-12).Cost utility analysis (European Quality of Life 5 Dimensions) after 12 months.Laboratory outcomes (baseline, 6 weeks and 6 months): hemoglobin, CA-125 and AMH in specific predefined centers.Pathology outcomes (6 weeks): pathological finding of uterus in hysterectomy group.

Also, imaging outcomes will be investigated in order to identify potential predictive parameters for therapy effect.

TVUS (baseline, 6 weeks and 6 months): imaging parameters described in Table 1, uterine size reduction and reduction of fibroid volume in case of concomitant fibroids. In specific predefined centers, we will measure vascular index (3D power Doppler).MRI (baseline and 6 months): imaging parameters described in Table 1, uterine size reduction, junctional zone reduction, infarction rate, reduction of fibroid volume in case of concomitant fibroids, presence of endometriosis.

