## Results

Inclusion of patients started in November 2015. The expected end date is November 2019. Data collection for the primary outcome will be expected to last until May 2020. Data collection concerning the secondary outcomes are expected two years following the last included patient. Analysis has not yet started as of this article’s submission.

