### Strengths and Limitations

This is the first randomized controlled trial evaluating effectiveness of UAE versus hysterectomy in patients with symptomatic adenomyosis. The QUESTA trial uses a web-based randomization program with the use of allocation concealment which reduces the chance of selection bias. The study is not blinded for the patient or health care worker which could possibly influence the outcomes. Blinding is impossible considering the nature of the treatments. Earlier studies reported on UAE being more cost-effective compared to hysterectomy, however these studies were conducted in patients with fibroids and mostly carried out through abdominal hysterectomies [31]. Over the years hysterectomy techniques have changed and the more cost-effective laparoscopy has become available. No studies have yet reported on cost effectiveness of UAE versus laparoscopic hysterectomy. We expect UAE to be more cost effective since the procedure itself is less expensive and recovery time is shorter [32], however we do expect consultation to be more frequent in the UAE group. We note that we allow all hysterectomy techniques in this study due to the intention to treat analysis. It will be registered and corrected for in analysis.

Disease specific questionnaires for adenomyosis have not yet been developed. Used questionnaires are validated in terms of quality of life, pain, heavy menstrual bleeding, sexual functioning, recovery, and allocation satisfaction and proved to be disease specific in the EMMY trial [13].

The follow-up in this trial is set at 24 months. This could be a limitation since 5- and 10-year follow-up of the EMMY trial showed additional hysterectomies in the UAE group [33,34]. Depending on the result of this trial a possibility to extend follow-up was included in the informed consent.

In the last 15 years, 30 cohorts and case series [15-26,35-52] described UAE in the treatment of symptomatic adenomoysis. The lack of level 1 evidence, heterogeneous particle use and UAE techniques make the development of a national guideline for standardized UAE in the treatment of adenomyosis challenging. We provide a mini-protocol on the usage of the standardized microspheres, however we do not provide a specific UAE technique protocol because we assume general UAE techniques will be followed [28]. In addition, we wish to maintain the intention to treat analysis of the Dutch population treated in the UAE centers.

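### The long-term analysis is timed at 12 months after the last procedure, but the final questionnaire is due at 24 months, and the cost horizon is given as both 12 months and 2 years

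*Protocol article*

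**What the plan says.** **Analysis timing.** The Statistical analysis section of the protocol article names two analyses. The first follows a database lock 6 months after the last procedure. The second is described as follows: "The long-term results (HRQOL and costs) will be analyzed 12 months after the last procedure, when the last patient returned her last questionnaire".

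**Follow-up schedule.** The Follow-up section sends questionnaires "at baseline, 6 weeks, 3 months, 6 months, 12 months and 24 months of follow-up". Outcomes measures states: "The primary outcome is quality of life at 6, 12 and 24 months after index procedure", and runs the secondary outcomes to 24 months as well. Strengths and Limitations states: "The follow-up in this trial is set at 24 months". The main Results section states: "Data collection concerning the secondary outcomes are expected two years following the last included patient". The abstract's Results paragraph likewise ends follow-up two years after the last inclusion.

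**Cost horizon.** The abstract's Methods paragraph promises "cost effectiveness during 2 years of follow-up". Outcomes measures lists: "Cost utility analysis (European Quality of Life 5 Dimensions) after 12 months".

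**The concern.** The sentence on the long-term analysis gives two triggers as if they were one: a date 12 months after the last procedure, and the return of the final questionnaire. On the article's own schedule these are a year apart. The article names no later analysis, so a team following the text cannot tell whether the long-term report should wait for the 24-month data. If it does not wait, those data are incomplete for the most recently treated patients.

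The two cost horizons raise a related problem. The horizon decides which costs are counted, and secondary hysterectomy is this trial's own definition of clinical failure. Leaving 12 months and 2 years both standing in an unblinded trial allows the choice to be made after the data are known.

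**Working it through.** **Inputs from the article**
- Final questionnaire: 24 months (Follow-up; Outcomes measures).
- Stated long-term analysis: 12 months after the last procedure (Statistical analysis).
- Inclusion from November 2015, with an expected end date of November 2019 (Results).
- 6-month data collection until May 2020 (Results).
- Total sample 96 (Sample size).

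**Check of the inputs**
- November 2019 + 6 months = May 2020, which matches the article. November 2019 is therefore read as the end of inclusion, giving 48 months of accrual.
- The total reproduces: 52 + 34 = 86, and 86 / 0.90 = 95.6, rounded up to 96.

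**Step 1: the two triggers.** Final questionnaire of the last patient = last procedure + 24 months, about November 2021. Stated analysis date = last procedure + 12 months, about November 2020. The gap is 24 − 12 = 12 months. (Both dates ignore any lag between inclusion and procedure.)

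**Step 2: who would lack 24-month data under the 12-month clause.** At that date, a patient has reached 24 months only if she was treated at least 12 months before the last procedure. With uniform accrual over A months, the share without 24-month data is 12/A.

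| Accrual assumption | Share | Patients of 96 |
|---|---|---|
| Uniform over 60 months | 12/60 = 20% | 19.2 |
| Uniform over 48 months | 12/48 = 25% | 24 |
| Uniform over 36 months | 12/36 = 33% | 32 |
| 15% treated in the last year | 15% | 14.4 |
| 50% treated in the last year | 50% | 48 |

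The article gives no accrual curve, so every row is an assumption. The 48-month row uses the article's own dates. Drop-out is ignored.

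**Step 3: what stays complete.** Every patient has reached 12 months by the stated date, so the 12-month questionnaires and 12-month costs are due for all. The 6-month analysis has its own lock and is untouched.

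**Step 4: costs.** The date in Statistical analysis says when the analysis is run. It does not say how many months of cost are counted per patient. Under the 48-month assumption, 100% − 25% = 75% of patients would already have a full 24 months at that date. The conflict over horizon is therefore between the abstract (2 years) and Outcomes measures (12 months).

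**The case against.** **The sentence carries its own safeguard.** If the questionnaire clause governs, the analysis waits until 24 months and no data are lost. The abstract and the main Results section, which both end data collection two years after the last inclusion, support that reading. This stands, and it limits the claim: loss is conditional on following the 12-month clause. It does not remove the contradiction, because the sentence gives the 12-month date just as plainly.

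**The loss would be mild.** Data missing because of a calendar cut depend on entry date, not on outcome, and the planned linear mixed model uses the repeated measures that are available. Barring a calendar trend, the effect on HRQOL is mainly lost precision at one time point. This also stands. It bears on severity, not on whether the text needs correcting.

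**Stronger readings that the article does not support**
- A reader might infer that the trial's primary result would be incomplete, since Outcomes measures lists 24 months under the primary outcome. But the abstract and Sample size fix the primary comparison at 6 months, and Results ends primary data collection in May 2020. The 24-month listing is a separate inconsistency.
- A reader might infer that all reinterventions in months 12 to 24 are dropped from the costs. The analysis date does not imply that (Step 4). Only a 12-month cost horizon would.
- A reader might infer that a 12-month horizon biases the cost result towards embolization. That is plausible, but the article gives no costs, utilities or reintervention rates for months 12 to 24. Strengths and Limitations cites later hysterectomies only from the 5- and 10-year follow-up of the earlier embolization-versus-hysterectomy trial. Neither the size nor the direction of a bias can be derived.

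**Conclusion.** The point holds as an internal contradiction that should be corrected. The two conditions for the long-term analysis are 12 months apart on the article's own schedule, and no analysis point is named at which the 24-month data are complete.

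If the 12-month clause is applied, about a quarter of patients (24 of 96) would lack 24-month data. This rests on uniform accrual and on reading November 2019 as the end of inclusion. The plausible range is 19 to 32 across the accrual lengths tried, and 14 to 48 if accrual was uneven.

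The cost horizon is stated in two incompatible ways. That supports a request to settle on one, but not a claim that either choice is biased. A 12-month horizon would leave out any reintervention costs in months 12 to 24; the consequence for the comparison is unknown from the article.

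**What to change.** 1. In Statistical analysis, replace the timing sentence with one that sets the long-term analysis at the point when the last patient has completed the 24-month questionnaire. Alternatively, keep the 12-month analysis, label it as a 12-month analysis, and add a separate 24-month analysis with its own timing.
2. State one main horizon for the cost analysis in advance, and use it in both the abstract and Outcomes measures. If the other horizon is kept, mark it as secondary.
3. Check that Follow-up, Outcomes measures, Statistical analysis, Results, and Strengths and Limitations then agree.

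The change is to wording only and uses data the trial already plans to collect. The cost is that the complete long-term report comes up to 12 months later than the 12-month clause would allow.
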